### Correlation analysis

Spearman correlation coefficients will be calculated to investigate the relationship between composite scores and word counts from scenario inputs and the corresponding generated outputs. This investigates whether the quantity of text correlates with the quality as perceived through the composite scores.

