### Data source

During the pre-defined study period, real-life clinical notes will be extracted retrospectively from the digital depository (in-house software) of the Department of Microbiology, Queen Mary Hospital (QMH), Hospital Authority, Hong Kong. Within the study period, 40 clinical notes derived from four clinical microbiologists [10 clinical notes per microbiologists; fellows (n =  2) and resident trainees (n =  2)] will be included consecutively.

For the inclusion criterion, only new in-patient consultation referrals received by the Department of Microbiology (QMH) during the study period will be included. As for exclusion criteria, duplicated consultations will be removed to limit redundancy and potential data skew. Follow-up assessments and reviews during the same clinical episode will be excluded to focus on initial management approach, diagnostic assessments, and treatment decisions. The inclusion and exclusion criteria are carefully designed to maintain clarity and data integrity and to ensure a well-defined analytical framework.

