### Blinding, randomisation and data compilation

The dataset will include 40 unique clinical scenarios, individually processed four AI chatbots (i.e., Claude 2, Gemini Pro, GPT-4.0 and cGPT-4), resulting in 160 total outputs. All study authors (except [name]) and human evaluators will be blinded to the original authors of the clinical scenarios, as well as the identity of GenAI model for the chatbot output.

To ensure objective assessments and minimise evaluator biases, all investigators, except [name], will be blinded to the clinical scenarios and chatbot outputs. Dual-level randomisation will be employed, where the clinical scenarios will be randomised before being inputted into the chatbots, and the corresponding AI-generated responses will be further randomised before being subjected to human evaluation. Randomised clinical scenarios and corresponding AI chatbot outputs will be uploaded onto the Qualtrics survey platform (Qualtrics, Utah, U.S.) for human evaluation and grading. Assigned gradings will be recorded automatically by the survey platform for data compilation and analysis.

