### Outcomes

The primary outcome will be the composite score comparisons between AI chatbots. Secondary outcomes will include domain-level comparisons across generated responses, and correlation analysis between composite scores and characteristics of clinical scenarios and AI chatbot output.

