### Composite score evaluation

Composite scores (range, 4-20) will be constructed by the summation of the mean scores of all four domains. Differences in mean composite scores among chatbots will be examined using one-way Analysis of Variance (ANOVA). Tukey’s Honest Significant Difference (HSD) test will be applied for post-hoc pairwise comparisons. [18,19] Paired t-tests will be used for within-group comparisons of composite scores between specialist and non-specialist evaluators.

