### Statistical significance

A p-value of less than 0.05 will be considered statistically significant.

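### The word-count correlations take no account of four chatbots answering each scenario; if the 160 outputs are pooled, the input-length p-value and the output-length rho can both mislead

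*Protocol article*

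**What the plan says.** The Outcomes section lists among the secondary outcomes a "correlation analysis between composite scores and characteristics of clinical scenarios and AI chatbot output". The Correlation analysis section gives the method: "Spearman correlation coefficients will be calculated to investigate the relationship between composite scores and word counts from scenario inputs and the corresponding generated outputs". It states the purpose as follows: "This investigates whether the quantity of text correlates with the quality as perceived through the composite scores".

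The data are fully crossed. The Data source section takes "40 clinical notes derived from four clinical microbiologists", and the section on blinding, randomisation and data compilation has every scenario processed by all four chatbots, "resulting in 160 total outputs". On the score, the plan says: "Composite scores (range, 4-20) will be constructed by the summation of the mean scores of all four domains". On significance it says: "A p-value of less than 0.05 will be considered statistically significant".

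The Correlation analysis section names no unit of analysis, no stratification by chatbot and no allowance for scenarios that recur.

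**The concern.** The usual Spearman p-value assumes independent pairs. In a 40 × 4 crossed design that assumption fails differently for the two word counts.

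- **Input length.** A scenario has one input word count but four composite scores. Over 160 rows, each predictor value is repeated four times. If some scenarios tend to score high or low whichever chatbot answers, the test claims more information than 40 scenarios carry.
- **Output length.** Each output has its own word count, but chatbots may differ in typical length and in typical score. The plan cannot assume equal scores, because score differences are its main question: "The primary outcome will be the composite score comparisons between AI chatbots". A pooled rho then combines which chatbot wrote the text with whether longer text from a given chatbot is rated higher.

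At stake is a published statement that more text goes with better perceived quality (or the reverse) when no chatbot shows such a relation, or a significant input-length result that 40 scenarios do not support.

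**Working it through.** **Inputs from the protocol article.** 40 scenarios; 4 chatbots; significance level 0.05. The plan's own count reproduces: 40 × 4 = 160.

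**Assumptions, none given in the document.** A two-sided test; one composite score per output; independent scenarios; normally distributed scores and log or raw lengths; the same-scenario correlation (ICC); the between-chatbot SDs. SDs are in units of the within-chatbot SD. Simulated rates use 10,000 replicates of 40 × 4 data with no true within-chatbot association.

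**(a) Input length, 160 rows pooled.** The design effect is 1 + (4 − 1) × ICC.

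- ICC 0.3: 1 + 3 × 0.3 = 1.9, so the effective n is 160 / 1.9 ≈ 84.
- ICC 0.7: 1 + 3 × 0.7 = 3.1, so the effective n is 160 / 3.1 ≈ 52.

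Chatbot score differences with SD b add b² to the score variance without adding to the covariance with input length. The null variance of rho is therefore scaled by roughly (1 + 3 × ICC) / (1 + b²), and the approximate type I error is 2 × [1 − Φ(1.96 / √scale)].

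- ICC 0.3, b = 0: scale 1.9; 1.96 / 1.378 = 1.42; error about 0.155.
- ICC 0.3, b = 0.5: scale 1.9 / 1.25 = 1.52; 1.96 / 1.233 = 1.59; error about 0.11.
- ICC 0.3, b = 1: scale 1.9 / 2 = 0.95, which is below 1, so the test is slightly conservative.

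Simulated type I error:

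| ICC | b = 0 | b = 0.5 | b = 1.0 |
|---|---|---|---|
| 0 | 0.049 | 0.028 | 0.005 |
| 0.1 | 0.084 | 0.052 | 0.013 |
| 0.3 | 0.155 | 0.108 | 0.039 |
| 0.5 | 0.207 | 0.164 | 0.069 |
| 0.7 | 0.273 | 0.206 | 0.103 |

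**(b) Output length, 160 rows pooled, ICC 0.3 for score and for length.** With chatbot SD L in length and Q in score, and the same ordering, the pooled correlation is about L × Q / [√(1 + L²) × √(1 + Q²)].

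- L = Q = 0.5: 0.25 / 1.25 = 0.20.
- L = Q = 1: 1 / 2 = 0.50.

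Simulated results:

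| L, Q | Mean rho, same / opposite order | Significant, same / opposite order | Significant, random order |
|---|---|---|---|
| 0, 0 | 0 / 0 | 0.077 / 0.082 | 0.077 |
| 0.5, 0.5 | +0.20 / −0.20 | 0.718 / 0.719 | 0.288 |
| 1, 1 | +0.52 / −0.52 | 1.0 / 1.0 | 0.709 |

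**After the change.** Input length against the scenario-mean score (n = 40) rejects in 0.048-0.053 of null runs. A single within-chatbot correlation (n = 40) rejects in 0.046-0.054. Four separate tests at 0.05, if independent, would have a family-wise error of 1 − 0.95⁴ = 0.185, which is a reason to combine them.

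**The case against.** The strongest reply is that the protocol never says the 160 outputs are pooled. The plural used for the coefficients would fit one coefficient per chatbot, and per-chatbot analyses at n = 40 have neither problem. That stands: pooling is an inference. It is still the most natural reading. The stated question is general, and no chatbot stratum is named, whereas the Domain-level evaluation section does say that its analysis is repeated for each domain. The one-way ANOVA and Kruskal-Wallis tests planned alongside also leave out the crossing. The plural is needed in any case for two word counts.

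A second reply is that a condensed article may leave the unit of analysis to a fuller document. That would answer a complaint about mere silence. Here a method is named, and in its ordinary form it does not fit the stated design.

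A third reply is that the stated aim is a marginal association, and if wordier chatbots score higher, a positive pooled rho describes that correctly. This also stands. The pooled output-length rho is a valid description of the 160 outputs. It is not evidence that longer text scores better within a chatbot, and its ordinary p-value does not test that.

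A reader might go further and infer that chatbot identity confounds both correlations. It cannot confound input length, which is identical for all four chatbots.

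**Conclusion.** The point holds in conditional form. If the 160 outputs are pooled, the input-length test treats 40 independent values as 160, and the output-length rho mixes between-chatbot with within-chatbot association.

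For ICCs of 0.3 to 0.7, input-length type I error is about 15-27% with no chatbot score differences and about 11-21% with a between-chatbot SD of 0.5. A reader might infer that this p-value is always too small. The figures do not support that: inflation needs a positive same-scenario correlation, and with a between-chatbot SD of 1 the error is below 5% at ICCs up to 0.3.

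For output length, with 0.5 SD differences in both length and score, rho is about ±0.20 and about 72% of tests are significant with no within-chatbot relation when the orderings align or oppose, against about 29% when the ordering is random.

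All these sizes rest on assumed ICCs and chatbot differences, so they show what could happen and do not predict this study's results. The impact is confined to a secondary outcome; the primary comparison of composite scores does not depend on these correlations. The change is worth making because it costs only wording.

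**What to change.** State the unit of analysis in the Correlation analysis section, for example:

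- **Input length:** Spearman correlation between each scenario's word count and its composite score averaged over the four chatbots, n = 40.
- **Output length:** Spearman correlation within each chatbot, n = 40 each, combined into one estimate. Equivalently, correlate ranks centred within chatbot. Take the interval from a bootstrap that resamples whole scenarios, because the four coefficients share the same scenarios. Make the combined estimate the one that is tested, so that four separate tests do not raise the family-wise error.
- **Pooled or between-chatbot association:** report as descriptive only, without a p-value; the between-chatbot part rests on four chatbots.

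If per-chatbot correlations were intended all along, saying so and adding the combination rule settles the matter.

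No new data are needed. The cost is a smaller effective n and wider intervals. The simulations cover the scenario-mean and single-chatbot tests; the combined estimate with its bootstrap was not simulated and should be checked when the analysis is programmed.

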### Statistical significance

A p-value of less than 0.05 will be considered statistically significant.

## Ethics and dissemination

The study protocol was reviewed and approved by the Institutional Review Board of the University of Hong Kong (HKU)/ Hospital Authority Hong Kong West Cluster (HKWC) – HKU/HA HKW IRB–UW 24-108. Informed consent was exempted.

The data collected in this study will be retrospective in nature, where they will be recorded for clinical purposes. All patient data will be fully de-identified prior to analysis, ensuring that privacy and confidentiality will not be breached. The findings of the study will be published in peer-reviewed academic journals and presented in abstract form at relevant scientific conferences.

### Status and timeline of the study

The study is currently in the evaluation phase, having successfully recruited a qualified panel of clinical microbiologists and infectious disease physicians in January 2024. These evaluators are actively reviewing the provided clinical scenarios. Preliminary analysis will be performed in March 2024. We aim to finalise data analysis by May 2024 and to have a complete report ready for peer review and publication by early 2025.

## Results and discussion

In this protocol, we hypothesise that analytical performance of AI chatbots in real-life clinical scenarios could be objectively measured using a standardised assessment protocol and graded by clinically experienced human evaluators. We also hypothesise that in the evaluation of structured clinical scenarios, AI chatbots primed with domain-specific knowledge in medical sciences could generate clinically relevant recommendations within the boundaries of the prompt template and the scope of the provided clinical data. We further hypothesise that AI chatbots could assist clinicians by providing accurate, comprehensive, and coherent analysis in clinical consultations, without posing medical harm.

In designing this study, we will employ several strategies to limit major biases. Recognising the critical importance of data quality, we will institute a rigorous data curation phase where clinical documents will be reviewed, cleaned, and standardised to ensure AI chatbot operates on high-integrity data. To address the potential for evaluator bias, we will adopt multiple blinding and randomisation procedures, including evaluator blinding, scenario randomisation and response randomisation. Moreover, we will select two diverse groups of evaluators to encompass a broad spectrum of clinical experiences, ensuring our study reflects the varied insights from both specialists and non-specialist doctors.

Nonetheless, there remain several key limitations that bear consideration when interpreting this study. One of the primary limitations is that this study does not accommodate for the inherent potential of continued learning and adaptation by AI chatbots over time. Advances in machine learning suggest that GenAI performances could be improved with continued exposure to clinical scenarios [22], a factor that our current zero-shot prompting protocol does not address. To refine the performance and reliability of LLMs, future research may consider longitudinal study designs or continuous evaluation methods to track the evolution of AI performance with the use of reinforcement learning and human feedback. [23]

Additionally, our protocol will rely on historical clinical data, which will not capture and reflect the dynamic and often unpredictable nature of real-time clinical decision-making. The inherent variability and fluidity of real-life clinical environments are difficult to replicate in a cross-sectional observational study, invariably limiting the generalisability of our findings.

The integrity of chatbot-generated responses is directly tied to the quality of inputted clinical data. [24] Inaccuracies, inconsistencies, or gaps in the original clinical documents may significantly compromise the performance of GenAI models and mask their true capabilities. Advances in natural language processing to automatically extract clinical data from electronic health records may help to mitigate some of these data quality challenges by providing more comprehensive inputs. [25]

Limited number of human evaluators represent another limitation. The study outcomes are dependent on the evaluators’ proficiency and their interpretation of the generated responses. Selected evaluators’ perspectives may not encapsulate the wide-ranging opinions and approaches that exist within the broader medical community, potentially leading to evaluations that do not fully capture the diversity of clinical judgments.

Finally, there are concerns regarding the evaluation scale utilised in this study, which has not been validated and may introduce subjective biases in the evaluation process.

To conclude, this study will represent a significant step towards understanding the analytical potentials of AI chatbots in the clinical setting. While the initial results will provide valuable insights into the capabilities and limitations of AI chatbots in processing and analysing clinical data in a structured manner, the limitations identified must be carefully considered.
